The immune response of pregnant women has not been extensively studied by trimester. Despite a trend toward lower immune responses in the first trimester and 6 weeks post-partum, Sperling et al. [17] did not find evidence that timing of vaccination significantly altered immune response to a monovalent H1N1 vaccine administered to 239 women during pregnancy or post-partum. Post vaccination anti-EBOV GP antibodies peak about 21 days post dose 2 and persist, with some waning, over a 1–2-year period. Fetuses/embryos in women vaccinated during earlier trimesters may be exposed to maternal antibodies for longer periods allowing more robust transfer of maternal antibodies trans-placentally. However, trans-placental antibody transfer generally gradually increases as pregnancy progresses [18, 19], and immunization of pregnant women is generally recommended in the second or third trimester to maximize the potential of passive transfer of maternal antibodies to the fetus. IgG transfer from the mother to the fetus can occur starting from gestational week 13 (end of the first trimester), although the majority of IgG transfer occurs during the third trimester. Additional forms of passive immune transfer occur postnatally and involve vaccine-induced IgA, IgG, and IgM being secreted into the colostrum and breast milk. There is evidence that maternal vaccination can inhibit neonatal humoral immune response to vaccination. However, this interference mainly impacts primary immunization and not subsequent booster immunizations. These topics are reviewed in Faucette et al. [20].

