**Secondary**	
• Assess safety **in pregnant women** randomized to receive the 2-dose Ebola vaccine regimen (Ad26.ZEBOV, MVA-BN-Filo group A) and in control women (unvaccinated pregnant women (group B))	• Frequency and relatedness of all SAEs in women from randomization until study end
• Assess safety **in neonates/infants born** to women randomized to receive the 2-dose Ebola vaccine regimen (Ad26.ZEBOV, MVA-BN-Filo (group A)) and in neonates/infants born to control women (unvaccinated pregnant women (group B))	• Frequency and relatedness of all SAEs in the newborns from birth until study end
• Assess the **reactogenicity** and unsolicited AEs of the 2-dose Ebola vaccine regimen (Ad26.ZEBOV, MVA-BN-Filo) in all vaccinated pregnant women (group A)	• Reactogenicity, defined as local and systemic solicited AEs occurring within 7 days after each dose, and unsolicited AEs within 28 days after each dose: ○ Frequency, grade, duration and causality for solicited systemic AEs and unsolicited AEs ○ Frequency, grade and duration for solicited local AEs
• Describe all pregnancy outcomes	• Pregnancy outcomes (example: normal delivery, Caesarian Section)
• Assess the **immunogenicity** of the 2-dose Ebola vaccine regimen (Ad26.ZEBOV, MVA-BN-Filo) in 150 pregnant women who are anticipated to receive both vaccine doses within the course of their pregnancy (a subset of the 1000 pregnant vaccinated women from group A) compared to 150 non-pregnant women vaccinated after delivery (a subset of group B)	• Anti-EBOV GP binding antibody concentrations, in ELISA units/mL (FANG ELISA) from: ○ Blood samples taken at pre-dose 1, 21 days post-dose 2, at delivery (group A subset only), and 1 year post-dose 1 ○ Cord blood if feasible from women in the group A subset
• Assess **persistence of maternal antibodies** in 75 infants born to women from the group A subset	• Anti-EBOV GP binding antibody concentrations, in ELISA units/mL (FANG ELISA) from a blood sample taken at 14 weeks of age

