### Participant timeline {13}

See Tables 2, 3, 4, and 5 for the participant schedule of activities and visit timeline.

**Table 2 Tab2:** Schedule of activities—women in group A

Visit #	1	2	3	4	5	6	7 ^a^	8	9	10	11^a^	EE
**Visit timing**^**p**^		**Dose 1**	**Dose 1** ** + 7 days**	**Dose 1 + ** **28 days**	**Dose 2**	**Dose 2 + ** **7 days**	**Dose 2 + ** **21 days**	**Dose 2 + ** **28 days**	**Pregnancy completion/** **termination**	**PP 1 + 42**	**Dose 1 + ** **365 days**	**Early** **Exit**
**Visit day and window**	** − 28 to 1**	**D1**	**D8 ± 3 days**	**D29 ± 7 days**	**D57** ** − 14 days, + 28 days**	**D64 ± 3 days**	**D78 ± 3 days**	**D85 ± 7 days**	**PP 1** ^b^ ** + 2 days**	**PP 43** ^c^ ** ± 14 days**	**Dose 1 + 365 ± 28 days**	
**Visit type**	Screening	**DOSE 1 group A**	Safety	Safety	**DOSE 2 group A**	Safety	Immuno	Safety	Safety and immuno	Safety	Safety and immuno	Early exit
Assessment of understanding	•											
Written informed consent (ICF) ^d^	•											
Inclusion/exclusion criteria	•	•										
Demographics ^**e**^	•											
Medical and obstetric history ^f^; pre-pregnancy and pre-study meds	•											
Physical examination ^f^	•				•					•		•
Obstetric exam ^f^	•	•			•				•			•^o^
Targeted physical exam ^f^		•	•	•		•	•	•			•	
Vital signs ^f^ incl. body temperature	•		•	•		•	•	•	•	•	•	•
Urine pregnancy test ^g^	•											
Hematology, chemistry ^g^	•											
Urine dipstick/urinalysis ^g^	•	•		•	•			•				
Syphilis, HIV, hepatitis B and C, malaria screening^g^	•											
Obstetric ultrasound ^h^	•	•^h^						•				•^o^
Biometric scan	•	•	•	•	•	•	•	•	•	•	•	•
Contact information	•	•	•	•	•	•	•	•	•	•	•	•
Randomization		•										
Pre-vaccination symptoms ^i^												
Vaccination		•			•							
30 min post-vaccination observation ^j^		•			•							
Solicited AE collection ^k^		•	•		•	•						
Unsolicited AE collection ^k^		•	•	•	•	•	•	•				
Distribution of participant diary, rulers and thermometers ^k^		•			•							
Participant diary review by site staff			•			•						
Adverse maternal, fetal outcomes		•	•	•	•	•	•	•	•	•		
SAE recording		•	•	•	•	•	•	•	•	•	•	•
Concomitant medications ^l^	•	•	•	•	•	•	•	•	•	•	•	•
Delivery history ^m^									•			
Post pregnancy physical examination ^m^									•			
Laboratory assessments^n^									•			
Acceptability questionnaire									•	•		•
Group A immunology subset supplemental procedures (*N* = 150)	**1**	**2**	**3**	**4**	**5**	**6**	**7**	**8**	**9**	**10**	**11**	

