^p^In case pregnancy completion/termination in a group A pregnant woman occurs prior to receipt of dose 2, visits 9 and 10 should be performed: visit 10 being relative to visit 9 (2 day window). Visit 5 (dose 2 vaccination with a window of – 14 days, + 28 days) should in this case be performed after visit 9, with visits 6 and 8 being relative to actual dose 2 receipt (visit 5). All of these visits should be captured in RedCap cloud in addition to source documentation. Reactogenicity data (diary completion) should still be performed following dose 2 for group A women that have a pregnancy completion/termination prior to receipt of dose 2

**Table 3 Tab3:** Schedule of activities—women in group B

Visit #	1	2	3	4	5	6	7	8	9^a^	10^n^	11 ^a^	EE
**Visit timing**^**p**^		**Randomiz-ation (D1)**	**D1 + 28 days**	**D1 + 56 days**	**D1 + 12 weeks**	**Pregnancy completion/** **termination**	**Dose 1**	**Dose 2**	**Dose 2 + ** **21 days**	**Dose 2 + ** **28 days**	**Dose 1 + ** **365 days**	**Early** **exit**
**Visit day and window**	**-28 to 1**	**D1**	**D29 ± 7 days**	**D57** ** − 14 days, + 28 days**	**D85 ± 7 days**	**PP 1** ^b^ ** + 2 days**	**PP 43** ^c^ ** + 28 days**	**PP 99** **-14 days, + 28 days**	**PP 120** ** ± 14 days**	**PP 127** ** ± 3 days**	**Dose 1 + 365 ± 28 days**	
**Visit type**	Screening	**Random-ization**	Safety	Safety	Safety	Safety and immuno	**DOSE 1 group B**	**DOSE 2 group B**	Safety and immuno	Safety	Safety and immuno	Early exit
Assessment of understanding	•											
Written informed consent (ICF) ^d^	•											
Inclusion/exclusion criteria	•	•										
Demographics ^**e**^	•											
Medical and obstetric history ^f^ and prestudy meds	•											
Physical examination ^f^	•						•	•				•
Obstetric exam ^f^	•	•				•						•^o^
Targeted physical examination ^f^		•	•	•	•				•	•	•	
Vital signs ^f^ incl. body temperature	•	•	•	•	•	•			•	•	•	•
Urine pregnancy test ^g^	•											
Hematology, chemistry ^g^	•											
Urine dipstick/urinalysis ^g^	•	•	•	•	•							
Syphilis, HIV, hepatitis B and C, malaria screening ^g^	•											
Obstetric ultrasound ^h^	•	•^h^			•							•^o^
Biometric scan		•	•	•	•	•	•	•	•	•	•	•
Contact information	•	•	•	•	•	•	•	•	•	•	•	•
Randomization		•										
Pre-vaccination symptoms^i^												
Vaccination							•	•				
30 min post-vaccination observation ^j^							•	•				
Adverse maternal, fetal outcomes		•	•	•	•	•	•					
SAE recording		•	•	•	•	•	•	•	•	•	•	•

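### Table 3 gives the group B day-21 serum a ±14-day window and Table 2 gives group A ±3 days, without explanation, so timing may distort one arm of the immunogenicity comparison

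*Protocol article*

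**What the plan says.** The immunogenicity objective in Table 1 sets 150 women vaccinated in pregnancy against a control subset: "compared to 150 non-pregnant women vaccinated after delivery (a subset of group B". The serum time points are "Blood samples taken at pre-dose 1, 21 days post-dose 2, at delivery (group A subset only), and 1 year post-dose 1". Pre-dose 1, day 21 after dose 2 and one year are therefore shared by both arms.

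The schedules place these visits as follows.

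| Visit | Group A (Table 2) | Group B (Table 3) |
|---|---|---|
| Dose 2 | "D57 − 14 days, + 28 days" | "PP 99 -14 days, + 28 days" |
| Dose 2 + 21 days, serum | D78 ± 3 days | PP 120 ± 14 days |
| Dose 2 + 28 days, no serum listed | D85 ± 7 days | PP 127 ± 3 days |
| One year, serum | "Dose 1 + 365 ± 28 days" | the same |

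On kinetics, the section on benefit-risk assessment says: "Post vaccination anti-EBOV GP antibodies peak about 21 days post dose 2 and persist, with some waning, over a 1–2-year period". It gives no rate of rise or decay.

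On anchoring, footnote p to Table 2 covers group A women whose pregnancy ends before dose 2, "with visits 6 and 8 being relative to actual dose 2 receipt (visit 5". It does not name visit 7, the day-21 serum. Table 3 has no matching statement for group B.

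**The concern.** The same nominal sample is held to a tight window in one arm and a loose one in the other, at the time point the article itself treats as the approximate peak. Near a peak, scatter in either direction tends to reduce the average. If only the comparator arm is scattered, its geometric mean tends to fall and its interval to widen, and the pregnant arm looks relatively better for a reason unrelated to pregnancy.

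The pattern in Table 3 is also odd in itself. The visit with the blood draw has the wide window, and the visit a week later, with no serum listed, has the narrow one. Group A is the other way round.

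This is the only between-arm immunogenicity objective, in a trial meant to support a change to the label on use in pregnancy. A later analysis can set aside an off-time sample but cannot turn it into a day-21 sample.

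**Working it through.** **1. Nominal timing.** Group A: 78 − 57 = 21 days. Group B: 120 − 99 = 21 days. Both arms aim at day 21, as labelled.

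**2. Permitted timing with dose 2 on its nominal day.**
- Group A: 21 ± 3 gives 18 to 24 days, a span of 6 days.
- Group B: 21 ± 14 gives 7 to 35 days, a span of 28 days.

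**3. Order of visits in group B.** The day-21 visit runs from PP 120 − 14 = 106 to PP 120 + 14 = 134. The day-28 visit runs from PP 124 to PP 130. The first window wholly contains the second, so the day-21 visit may come after the day-28 visit.

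**4. Literal calendar reading.** The windows are written in study or post-partum days, while dose 2 may move by −14 to +28 days (D43 to D85 in A, PP 85 to PP 127 in B).
- Group A: 75 − 85 = −10 to 81 − 43 = +38 days after dose 2.
- Group B: 106 − 127 = −21 to 134 − 85 = +49 days after dose 2.

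On this reading neither arm is tied to dose 2.

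**5. Illustration of size. These kinetics are assumed and are not in the article.** Let the log concentration rise linearly by a factor F from day 7 to day 21, then decay with half-life H days. Assume no true difference between arms and visits spread evenly over each window. For a window of ±w days, half the samples are early and half late, each on average w/2 days from the peak. The mean log loss is

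L(w) = (w/4) × (ln F/14 + ln 2/H)

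and the spurious A/B ratio is exp[L(14) − L(3)] = exp[(11/4) × (ln F/14 + ln 2/H)].

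Example, F = 2 and H = 30: (11/4) × (0.0495 + 0.0231) = 0.200, and exp(0.200) = 1.22.

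| F | Ratio, H from 120 down to 30 days |
|---|---|
| 1 (flat before the peak) | 1.02 to 1.07 |
| 2 | 1.16 to 1.22 |
| 4 | 1.33 to 1.40 |
| 10 | 1.60 to 1.68 |

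If group B visits in practice fall within ±7 days, the factor 11/4 becomes (7 − 3)/4 = 1, and the same inputs give 1.01 to 1.21. If they fall within ±3 days, the ratio is 1.00.

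**6. Direction.** An even spread always gives a ratio above 1 in this model, but a one-sided spread need not. With all group B samples late (days 21 to 35), the ratio runs from 0.92 to 1.16. With all of them early (days 7 to 21), it runs from 0.98 to 2.78. The upward bias is likely under scatter on both sides of the peak, but it is not certain.

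**The case against.** The strongest reply is that a window permits scatter and does not show it. Both arms share the 21-day target, and staff may have kept close to it. This stands. A reader might infer that the two arms are in fact compared at different points of the antibody curve, but the article gives no actual visit dates and so cannot support that.

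The loose calendar limits are not peculiar to group B. Group A's literal range is −10 to +38 days, and its day-21 window (D75 to D81) also overlaps its day-28 window (D78 to D92). The visit-timing row ties both visits to dose 2, so a post-dose-2 sample taken before dose 2 is not a fair working reading. This stands too. The calendar extremes show that the anchoring needs correction in both arms, not that group B alone is uncontrolled.

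A reader might also infer that the per-protocol immunogenicity set keeps every in-window sample. The article says only that this set excludes major deviations expected to affect immunogenicity, and it refers detailed methods to the SAP, which is not at hand. Analysis windows may be set there.

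Finally, the article says antibodies persist with some waning, so late samples may lose little and early ones would matter most. The analysis is descriptive, with no test or power to damage, and day 21 is one of three shared time points.

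None of this explains why the same sample has unequal windows, or why the day-21 window surrounds the day-28 visit.

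**Conclusion.** The discrepancy is real and rests on the two schedules alone: 18 to 24 days against 7 to 35 days after a nominal dose 2, unexplained, with group B's window swallowing its own next visit. Whether it is a slip or a choice, the document does not settle.

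Wider scatter in group B alone may lower its geometric mean at day 21 and so flatter the response in pregnancy. The size is unknown. The range of about 1.02 to 1.7 rests wholly on assumed kinetics (F from 1 to 10, H from 30 to 120 days) and on visits filling the whole window; with good attendance the artefact is about 1.0.

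This is a moderate issue. It affects one of three shared time points of a descriptive secondary outcome, in a subset of 300 women. The one-year sample has equal windows, and the primary safety outcomes are untouched.

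**What to change.** Reconcile Tables 2 and 3 by defining the day-21 serum in both arms from the actual date of dose 2, with one common window, for example the ±3 days already used in group A. State that it precedes the day-28 visit. This concerns the timing of a blood draw only; the dose windows are not part of the change.

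Recruitment was due to end about January 2022, so some samples may already have been drawn. For those, base the day-21 comparison on samples inside the common window, using the actual sampling day, and show all samples as a sensitivity analysis. If the SAP already has such a rule, it needs only to be aligned with the corrected tables.

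The cost is a formal amendment with ethics approval, as the section on protocol amendments {25} requires, and the loss of some group B samples from the main day-21 comparison.

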**Exploratory**	
• Assess acceptability of an Ebola vaccine among healthy pregnant women (group A)	• Description of vaccine acceptability among vaccinees after they receive both doses • Evaluation of factors associated with study enrollment (defined as the proportion of eligible women who agree to sign the informed consent)
• Assess presence of maternal antibodies in breast milk in 50 women from group A and 10 controls (women from group B prior to vaccination)	• Evaluation of Anti-EBOV GP binding antibodies depending on availability of assays; in a sample of breast milk at 6 weeks post-delivery

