**Methods:**

A total of 2000 adult (≥ 18 years of age) pregnant women will be enrolled from antenatal care facilities in Western Rwanda and randomized (1:1) to receive the 2-dose Ebola vaccine regimen (Ad26.ZEBOV, MVA-BN-Filo (group A)) or control (unvaccinated pregnant women (group B)). The primary objectives are to (1) assess adverse maternal/fetal outcomes in randomized pregnant women up to 1.5 months after delivery and (2) assess adverse neonatal/infant outcomes in neonates/infants born to randomized women up to 3.5 months after birth. The frequency and relatedness of all serious adverse events in women and newborns from randomization or birth, respectively, until study end will be reported. The reactogenicity and unsolicited adverse events of the 2-dose Ebola vaccine regimen in all vaccinated pregnant women (group A) will be reported. We will also assess the immunogenicity of the 2-dose Ebola vaccine regimen in 150 pregnant women who are anticipated to receive both vaccine doses within the course of their pregnancy (a subset of the 1000 pregnant vaccinated women from group A) compared to 150 non-pregnant women vaccinated after delivery (a subset of group B). The persistence of maternal antibodies in 75 infants born to women from the group A subset will be assessed. Exploratory analyses include assessment of acceptability of the 2-dose Ebola vaccine regimen among group A and assessment of maternal antibodies in breast milk in 50 women from group A and 10 controls (women from group B prior to vaccination).

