### Criteria for discontinuing or modifying allocated interventions {11b}

Participants will be withdrawn from study vaccine administration for the reasons listed below. These participants must not receive any additional dose of study vaccine but should enter the follow-up phase with assessments of safety and immunogenicity. Dose modification is not applicable in this study.Any related AEs, worsening of health status or intercurrent illnesses that, in the opinion of the investigator, required discontinuation from study vaccineConfirmed EVDAnaphylactic reaction following vaccinationInjection site ulceration, abscess, or necrosis considered to be related to study vaccineGeneralized urticaria within 72 h of vaccination considered to be related to study vaccineSAEs or other potentially life-threatening (grade 4) event that is determined to be related to study vaccineChronic or recurrent use of immunosuppressants (after discussion with the sponsor)

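### The acceptability endpoint is worded for women who received both doses, which is narrower than its group A objective and does not match the questionnaire schedule

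*Protocol article*

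**What the plan says.** Table 1 (Exploratory) gives the objective as "Assess acceptability of an Ebola vaccine among healthy pregnant women (group A"). The first endpoint set against it is "Description of vaccine acceptability among vaccinees after they receive both doses". The abstract (Methods) states the population as the objective does: "Exploratory analyses include assessment of acceptability of the 2-dose Ebola vaccine regimen among group A".

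A second endpoint under the same objective concerns uptake of the study itself: "Evaluation of factors associated with study enrollment (defined as the proportion of eligible women who agree to sign the informed consent").

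The row "Acceptability questionnaire" in Table 2 (group A schedule) is marked at visit 9 (pregnancy completion or termination), visit 10 (six weeks post-partum) and Early Exit.

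Two further places show who attends those visits. Of women withdrawn from vaccination, the section on discontinuing or modifying interventions {11b} says: "These participants must not receive any additional dose of study vaccine but should enter the follow-up phase with assessments of safety and immunogenicity". Footnote p to Table 2 says: "In case pregnancy completion/termination in a group A pregnant woman occurs prior to receipt of dose 2, visits 9 and 10 should be performed". It then places the dose 2 visit after visit 9.

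**The concern.** The objective asks how acceptable the regimen is to group A. Coming back for dose 2 is itself partly a sign of acceptance. A summary limited to women who came back therefore selects on an event after randomization that is likely to be related to the answer. Women who disliked dose 1 and declined dose 2 may be the most informative respondents. The schedule collects their questionnaire, but the endpoint as worded has no place for it.

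At stake is a descriptive figure that answers a narrower question than the one posed and that may look better than group A as a whole would. No hypothesis test, primary outcome or safety summary depends on it.

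**Working it through.** The document states no acceptability figure and no expected rate of non-completion, so there is nothing to reproduce. The check has two parts: a comparison of the passages, and a sensitivity calculation on assumed inputs.

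**Passages side by side**

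| Place | Who is covered |
|---|---|
| Table 1, objective | Group A, no dose condition |
| Abstract, Methods | Group A, no dose condition |
| Table 1, first endpoint | Vaccinees, after both doses |
| Table 2, questionnaire row | Any group A woman at visit 9, visit 10 or Early Exit |
| Section {11b} | Women withdrawn from vaccination stay in follow-up, so they can reach visits 9 and 10 |
| Table 2, footnote p | Women who deliver before dose 2 still have visits 9 and 10 |

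The endpoint is the only entry that requires both doses.

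**Does reading the phrase as timing resolve it?** Suppose it means only that the questionnaire is given once both doses are in.

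- Early Exit can fall before dose 2.
- Under footnote p, visit 9 falls before dose 2 in any woman who delivers first.
- Visit 10 can fall on either side. Take delivery on day 40 as an example. Visit 10 is due 42 days later, on day 82, with a window of ±14 days: day 68 to day 96. Dose 2 is due on day 57 with a window of −14 to +28 days: day 43 to day 85. The windows overlap, so either order is possible.

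The wording and the schedule therefore disagree on both readings.

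**How large could the effect be?** Let d be the share of responding group A women without dose 2, p_c the proportion of completers who find the vaccine acceptable, and p_n the same proportion among the others. Then:

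- all responding group A women = (1 − d) × p_c + d × p_n
- excess of the completers-only figure = d × (p_c − p_n)

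Every input below is an assumption. So is the treatment of acceptability as a yes/no proportion, since the protocol promises only a description. With p_c = 95%, the excess in percentage points is:

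| d | p_n = 95% | p_n = 70% | p_n = 50% | p_n = 0% (ceiling) |
|---|---|---|---|---|
| 2% | 0 | 0.5 | 0.9 | 1.9 |
| 5% | 0 | 1.25 | 2.25 | 4.75 |
| 10% | 0 | 2.5 | 4.5 | 9.5 |
| 20% | 0 | 5.0 | 9.0 | 19.0 |

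Example: with d = 10% and p_n = 50%, the full figure is 0.90 × 0.95 + 0.10 × 0.50 = 0.905. The completers-only figure is 0.95, an excess of 4.5 points.

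**The case against.** The strongest reply is that this is loose wording, not a filter. The objective and the abstract both name group A, no completers-only analysis set is defined, and nothing says that questionnaires from one-dose women will be dropped. Marking the questionnaire at Early Exit suggests that those answers are wanted. The handling of an exploratory questionnaire may also be set out in the analysis plan, which is not shown. This stands to the extent that discarding of answers is an inference from the endpoint wording and not a stated rule. It does not remove the mismatch, because the timing reading also conflicts with the schedule.

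A reader might also infer that women who refuse the vaccine are left out altogether. The documents do not support that. The second endpoint counts eligible women who decline consent in its denominator, so only declining dose 2 is in question here.

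Not every woman without dose 2 has refused it. Section {11b} lists medical grounds such as related adverse events, intercurrent illness and anaphylaxis, and such women may still regard the vaccine well. Women who deliver before dose 2 remain scheduled to receive it. For them the issue is the timing of the answer, not selection.

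Finally, the Statistical methods section {20a} already plans to report the number and percentage receiving two doses by arm, so a reader would have the completion rate. That is correct, but the rate does not convey the views of women who stopped.

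**Conclusion.** The inconsistency is real. The endpoint wording covers fewer women than its objective and fewer than the questionnaire schedule reaches. Followed literally, it conditions on receipt of dose 2 and may give too favourable a summary.

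It would be tempting to conclude that acceptability is overstated. The document does not establish that. It gives neither the share of women without dose 2 nor their views, and the excess is zero if they answer as completers do. Under the assumed inputs with completers at 95%, others at 50% to 95% and 2% to 20% lacking dose 2, the excess runs from 0 to 9 points. Its ceiling is 19 points, reached only if 20% lack dose 2 and none of them finds the vaccine acceptable.

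The point is minor. The endpoint is exploratory and descriptive, and no conclusion on safety or immunogenicity rests on it.

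**What to change.** Reword the first acceptability endpoint so that its population is all group A women who received dose 1 and completed a questionnaire at visit 9, visit 10 or Early Exit. Then:

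- Report results by the number of doses received at the time of the questionnaire, which also deals with women who deliver before dose 2.
- Place them beside the two-dose completion rate already planned.
- Give the recorded reasons for not receiving dose 2, with refusal separated from medical withdrawal.
- Keep the two-dose subset as its own row, so that nothing now planned is lost.

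The cost is a change of endpoint wording and a few table rows. No new visit or questionnaire is needed. One limit remains: women who cannot be reached and are counted as withdrawn may leave no questionnaire, so their number should be shown beside the result.
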